#### Statistical software

SAS studio, ver 3.7.

#### Interim analyses {21b}

For interim analyses, there will be used an alternative time point of 7 days instead of 90 days for the primary and selected secondary outcomes (death). Interim analysis after inclusion of 400 patients is planned.

#### Methods for additional analyses (e.g., subgroup analyses) {20b}

Predefined subgroup analyses including the following predefined variables will be performed and presented as a forest plot
SexAge above the median age for the populationKnown renal failure (defined as eGFR < 30 ml/min or current renal placement therapy) at time of cardiac arrestKnown hypertension at time of cardiac arrestKnown chronic obstructive pulmonary disease at time of cardiac arrestShockable primary rhythmSuspected STEMI as cause of cardiac arrestSite

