### Objectives {7}

### Primary objective

To evaluate the superiority of one of the two blood pressure targets investigated: approximately 63 mmHg and approximately 77 mmHg and, separately, superiority of on the two PaO_2_ targets (restrictive vs. liberal oxygenation) with regard to a combined endpoint of time to:
Death from any cause orDischarge from hospital in a state of Cerebral Performance category 3 or 4, whichever occurs first

The hospital stay includes tertiary center as well as the local hospital and or specialized hospital-based neurological rehabilitation.

A stratified analysis by the following predefined design variables will also be performed: sex, age above median, pre-arrest renal failure GFR (< 30 ml/min or current renal replacement therapy), pre-arrest hypertension, pre-arrest chronic obstructive pulmonary disease, shockable primary rhythm, and suspected STEMI on initial ECG.

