### Sample size {14}

Sample size estimation is based on blinded BP target allocation and on the assumption that no interaction with the oxygen intervention exists.

The combined primary outcome is time to death or hospital discharge in a state of CPC 3 or 4. We are planning a study with 400 experimental subjects, 400 control subjects, an accrual interval of 48 months, and additional follow-up after the accrual interval of 3 months. Prior data indicate the 6-month mortality is 33% overall. Assuming a mortality of 28% in the superior group compared to 38% in the inferior groups, we will need to include 732 patients in total or 846 patients in total to achieve a power of 0.8 and 0.9, respectively. The type I error probability associated with this test of the null hypothesis that the experimental and control survival curves are equal is 0.05.

Loss of final measurement is expected, but from the experience from the previous trial, the number of missing follow-up assessments is small (< 5%) and will not result in an increase of the number of patients needed.

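### Age as an effect modifier is examined only by a split at the sample median, which wastes information if the effect changes smoothly with age; the STEMI subgroup is also worded in two ways

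*Protocol article*

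**What the plan says.** The protocol article lists its subgroups twice.

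- **Objectives {7}, Primary objective.** A stratified analysis by predefined design variables. Age enters as "age above median" and STEMI as "suspected STEMI on initial ECG". Site is not listed.
- **Methods for additional analyses {20b}.** Predefined subgroup analyses that "will be performed and presented as a forest plot". Age enters as age "above the median age for the" population. STEMI enters as suspected "STEMI as cause of cardiac" arrest. Site is listed.

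The other items (sex, renal failure, hypertension, chronic obstructive pulmonary disease, shockable rhythm) agree in substance. Neither section mentions a model with age as a continuous modifier. The article gives no age distribution and no expected form of any age interaction.

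**The concern.** **Age.** A median split treats patients just either side of the cut as different and everyone on one side as alike. If the effect of the blood pressure or oxygen target changes gradually with age, the split tests that change with less power than the recorded ages allow. A forest plot with two overlapping age rows may then be read as evidence that the effect is consistent.

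**STEMI.** An ECG finding and an attributed cause are not the same variable. A patient can have a suspected STEMI on the tracing without it being held to be the cause of the arrest, and the reverse is possible. The Dissemination plans section sends the two interventions to two separate papers, so each paper could follow a different section and still claim a predefined subgroup.

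**Working it through.** **The plan's own figure.** There is none to reproduce: the article gives no figure for the precision of any subgroup analysis.

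**Inputs from the document**
- Planned size: "400 experimental subjects, 400 control subjects", so N = 800 (Sample size {14}).
- Planned effect: "Assuming a mortality of 28% in the superior group compared to 38% in the inferior groups" (same section), so about one third of patients have an event.

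**Inputs assumed**
- The shape of the age distribution, and an interaction that is linear in age on the log hazard scale.

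**Step 1: information kept by the split.** For a linear interaction, the share kept when age X is replaced by D = 1 if X is above the median is approximately corr(X, D)². D has variance 1/4.
- Normal X (SD 1): cov = 1/√(2π) = 0.399; corr = 0.399/0.5 = 0.798; corr² = 2/π = 0.637. Loss 0.363.
- Uniform X on 0 to 1: cov = 3/8 − 1/4 = 1/8; variance 1/12; corr² = (1/64)/(1/48) = 0.75. Loss 0.25.
- Laplace X (scale 1): cov = 1/2; variance 2; corr² = 0.25/0.5 = 0.50. Loss 0.50.
- By simulation: normal with mean 62 and SD 14 truncated at 18 (assumed values), loss 0.36; left-skewed Beta(5,2), loss 0.35.

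In patients, for this question only: 0.363 × 800 = about 290 under normality, with a range of 0.25 × 800 = 200 to 0.50 × 800 = 400.

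**Step 2: when the assumption fails.** If the true modification is a step at the median, D is the correct variable and the split loses nothing. Because corr² is symmetric, a linear term in normal age would then be the one to lose about 36%.

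**Step 3: check in a Cox model.** With N = 800, normal age, about one third events and an interaction of 0.3 in log hazard ratio per SD of age, the loss measured from mean z statistics was 41% to 42% (simulation intervals together about 38% to 46%). That is a little above the formula and inside the 25–50% range.

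**Step 4: power under assumed interactions.** N = 800, 90 days, baseline hazard 0.0045 per day, age log hazard ratio 0.5 per SD, 400 replicates:

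| Interaction per SD of age | Continuous age | Median split |
|---|---|---|
| 0 | 0.06 | 0.06 |
| 0.25 | 0.54 | 0.29 |
| 0.35 | 0.80 | 0.47 |

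A separate run of the two non-null scenarios gave 0.54 against 0.30 and 0.82 against 0.50.

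For scale, the planned main effect is ln[−ln(0.62)/−ln(0.72)] = ln(0.478/0.3285) = 0.375. An interaction of 0.35 per SD is therefore nearly as large as the whole planned treatment effect.

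**Step 5: STEMI, side by side.** Both wordings contain the word suspected. The Objectives wording ties the suspicion to one tracing. The wording in {20b} ties it to cause and sets no time for the judgement. The two are different criteria, but the article does not allow an estimate of how many patients they would class differently.

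**The case against.** **A forest plot needs categories, and a continuous model is a matter for the analysis plan.** This stands in part. The full protocol and any analysis plan are not shown, and {20b} introduces its list in a way that need not be exhaustive. So the word only applies to this article. But the median split is a choice the article makes twice, and adding a better-powered test beside it conflicts with nothing.

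**The cut is not a source of bias.** This stands. A reader might infer that a cut unknown until enrolment ends leaves room for choice. The rule is fixed in advance, and the median of a baseline variable does not depend on outcome or allocation.

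**The size is assumed.** This also stands. The 36% needs normal age and a linear interaction, and the simulated interactions come from nowhere in the document. At 0.25 per SD even the continuous test misses nearly half of true interactions, because the trial was not sized for them. The remedy improves the test without making it strong.

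**The STEMI harm is speculative.** A reader might infer that the cause-based subgroup would be settled after angiography, hence after randomisation, and could differ by arm. The document does not support this. The item in {20b} says suspected, presumed cause is already judged at screening under the eligibility criteria, and no section says when STEMI membership is assigned. For blood pressure, staff are blinded to allocation. Oxygenation is open label, so timing could matter there, but nothing shows a late assignment. What remains is the conflict of wording.

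**Conclusion.** The point holds as a modest one about efficiency and consistency in a secondary analysis. The primary analysis is unaffected.

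- **Age.** In this article effect modification by age is examined only through a median split. Under roughly normal age and a linear interaction this costs about 36% of the information on that interaction, with about 25–50% across the age shapes tried and none for a step at the median. It is a loss of power, not a bias.
- **STEMI.** The two sections use different criteria for the same predefined subgroup and must be reconciled. The number of patients affected cannot be derived from the document.
- **Site.** Its presence in one list only is an editorial mismatch.

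**What to change.** - For each of the two interventions, add a Cox model for the primary outcome with treatment, age and a continuous treatment-by-age term, linear or with a spline fixed in advance. Report the interaction estimate and its p value. Keep the median split for the forest plot only.
- Use the initial-ECG definition of STEMI in both sections, because it is fixed at baseline and needs no later judgement of cause.
- Make the two subgroup lists identical, including whether Site belongs.

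The cost is one extra model per intervention, a sentence or two of text and no new data. The downside is an assumed functional form: a linear term is the weaker test if the true change is a step. The changes should be made before unblinding, which the Trial status section places after the 90-day follow-up. Choosing between the two STEMI definitions once results are known would be a data-driven choice.

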#### Methods in analysis to handle protocol non-adherence and any statistical methods to handle missing data {20c}

Trial sites will be asked to complete all CRFs and other forms if missing data is found in the electronic database. Missing data will be reported in the publication. More than 5% missing data will result in multiple imputation with the creation of 5–10 imputed datasets to be analyzed separately and the aggregated into one estimate of intervention effect on the primary and secondary outcomes [59, 60]. Analyses will be performed according to the modified intention to treat principle with patients lost to follow-up included in the denominator.

#### Plan to give access to the full protocol, participant-level data, and statistical code {31c}

Access to the protocol will be given on request. Access to participant-level data will be given only if the data regulation authorities permit.

#### Adverse event reporting and harms {22}

Adverse reporting is performed according to good clinical practice principles. However, since death is frequent, the scientific ethics committee is only informed of the number of deaths and other adverse events annually, unless the adverse are suspected to be directly related to the protocolized interventions.

#### Frequency and plans for auditing trial conduct {23}

Planned interim analyses have been performed after 200 or 400 patients have been included in the trial and the DSMB has given their advice directly to the Steering committee. A charter for the DSMB has been published, but the DSMB will have unlimited access to data if requested.

#### Plans for communicating important protocol amendments to relevant parties (e.g., trial participants, ethical committees) {25}

Protocol revisions have been performed and have been communicated to the ethics committee according to their requirements. No changes in the current protocol are planned. Any deviations from the protocol will be fully documented using a breach report form. No updates to the protocol in the clinical trial registry https://www.clinicaltrials.gov/ct2/show/NCT03141099 are planned, other than updating the trial status.

#### Dissemination plans {31a}

The results of the trial will be published, regardless of being positive, negative, or inconclusive. The result of the two major interventions (blood pressure and oxygenation targets) will be published in two separate scientific papers.

The trial will be analyzed by the steering group (SG) and the results interpreted by the SG with data coded as “A” and “1” and the allocation of the patients will not be revealed until the SG agrees on the statistical analysis and drafts a conclusion based on the primary outcome. A manuscript will be drafted at a closed meeting by a predefined writing group consisting of the SG members. The final manuscript will be submitted to a peer-reviewed international journal. Authorship will be granted using the Vancouver definitions and depending on personal involvement. The author list including steering group members and others who fulfilled the Vancouver criteria as well as the chair of the DSMB will be offered co-authorships. Centers recruiting ≥50 patients will be entitled to one name (additional names) per 50 patients randomized in the trial. A reference to an appendix with all sites, site investigators, and number of patients enrolled will be made.

## Discussion

### Blood pressure intervention

Blood pressure is an easily accessible parameter in describing and monitoring the patients’ hemodynamics and is thus a central part of the monitoring in most patients admitted to critical care. While blood pressure alone does not describe perfusion or oxygen delivery, many consider blood pressure as one of the main goals in managing patients with critical conditions, including post-cardiac arrest [19, 20]. A clinical study assessed the existence of the cerebral autoregulation in post-cardiac arrest victims, by manipulating blood pressure by administration of nor-epinephrine in 18 patients, finding an impaired cerebral autoregulation in 44% of the patients [61]. The same study identified a lower limit of cerebral autoregulation at 114 mmHg (range 80–120 mmHg) in patients with preserved autoregulation, compared to 76 mmHg in normal volunteers, indicating that current practice targets may be sub-optimal [61]. Impaired cerebrovascular autoregulation has also been found to be associated with poor neurological and clinical outcomes in a small study [62]. The clinical consequences of targeting blood pressures below the limits of cerebral autoregulation in the management of post-cardiac arrest patients remain to be resolved.

A systematic review concluded from 9 observational studies that higher blood pressure is associated with improved neurological outcome after cardiac arrest and acknowledging a significant risk of bias, not only due to the observational study designs, but also due to a significant heterogeneity between studies [63]. Blood pressure has been measured as mean arterial pressure (MAP), systolic blood pressure (SBP), or a time-weighted average of MAP (TWA-MAP); outcomes varied for neurological outcome and mortality [63].

Previous studies have reported a significant higher value for MAP during TTM than what seems to be current practice. The Bernard trial of 2002 reported mean MAP values ranging from 88 to 108 during ICU admission [16], whereas a more contemporary trial, the TTM trial, found MAP ranging from 75 to 80 mmHg during TTM [28]. This study found a steep increase in risk of death for MAP below 65 and only a modest protective effect of higher blood pressure values [28]. Furthermore, a consistent association of increasing need for vasopressors and poor neurological outcome or mortality has been reported [28].

Two recent, relatively small clinical open-label prospective trials have investigated two different targets for blood pressure during targeted temperature management since the present trial was initiated. Ameloot et al. compared targeting a MAP of 85–100 to 65 mmHg, finding no difference in the primary outcome of the extent of neurological injury on MRI of the brain and similar fraction of patients with good neurological outcome [22]. A second study by Jakkula et al. compared a low-normal blood pressure of 65–75 mmHg to high-normal blood pressure 80–100 mmHg, finding no differences in NSE levels at 48 h and no differences in the clinical secondary outcomes [23].

The current European Resuscitation Council guidelines suggest a target blood pressure sufficient for maintaining a urine output of 0.5 ml/kg/h and to avoid blood pressure < 65 mmHg [20], whereas the American Heart Association guidelines suggest targeting a MAP greater than 65 mmHg or greater than 90 mmHg systolic (class IIa, LOE B-NR) [19]. As part of a survey distributed among the participating centers in the TTM trial, sites reported a standard blood target varying between MAP of 60 and 75 mmHg (personal communication).

Thus, the current body of evidence supporting MAP targets of 65–75 mmHg is very weak, and a clinical equipoise of optimal target blood pressure in the interval of approximately 65 to 75 mmHg or higher exists.

### Oxygenation intervention

Preclinical data suggest that hyperoxia increases cerebral damage and neurological dysfunction following brain ischemia. Most data originates from cardiac arrest models in which a no-flow state is induced and cerebral injury or neurological dysfunction is assessed [20–22]. Fairly small RCTs in humans have found increased levels of NSE but not S-100B in patients randomized to FiO_2_ = 100% compared to FiO_2_ = 30% [23]. Furthermore, a post-analysis of patients mechanically ventilated after suffering non-traumatic brain injury seems to have a poorer outcome with high oxygenation targets [35].

Hyperoxia during and after ischemia has been investigated in several settings, and a final consensus of its benefits and hazards has yet to be established. In the following, the term hyperoxia is used in situations where the FiO_2_ is increased to levels above 50% for simplicity.

Hyperoxia may increase the risk of developing lung injury (hyperoxia-induced lung injury (HALI)), which carries a high morbidity and mortality. However, this condition seems to require several days of extremely high FiO_2_ to be significant and various ventilation modes may have a significant impact as well [24]. The risk of HALI associated with shorter periods of hyperoxia seems small.

Ischemia-reperfusion injury has been investigated in smaller studies only in relation to circulatory bypass with no significant impact on the magnitude of increase in biomarkers related to cardiac injury according to a review by [25]. Oxygen administration during transport for primary PCI in patients with ST segment myocardial infarction has recently been associated with increased release of creatinine kinases and larger final infarcts size on cardiac magnetic resonance imaging [26]. The impact of shorter courses of oxygen supplement during weaning from circulatory bypass has yet to be investigated. A direct influence of hyperoxia with an increase in systemic vascular resistance has also been suggested, and hyperoxia may not be associated with improved tissue oxygenation [27], while the clinical effects of this finding remain to be understood [25].

A recent systematic review and meta-analysis suggested that the risk of surgical site infections may be reduced with hyperoxia [28]. However, a larger RCT in abdominal surgery found an increased mortality with hyperoxia, in particular in patients undergoing surgery for malignancies [29].

In summary, hyperoxia may reduce risks associated with surgery and critical illnesses with regard to surgical site infections and possibly reperfusion injury, whereas the effects on overall benefit in terms of mortality may be detrimental. Further research is needed, and for the time being equipoise with regard to the benefits of different targets for oxygenation. Most patients will require some degree of oxygen supplement when lungs are ventilated after OHCA; hence, this study pragmatically studies low normal, i.e., “restrictive” PaO_2_ of 9–10 kPa (target 9.5 kPa), and high normal, i.e., “liberal” PaO_2_ of 13–14 kPa (target 13.5 mmHg). FiO_2_, PEEP, and lung recruitment maneuvers for maintaining the assigned PaO_2_ are left at the discretion of the treating physician.

## Trial status

Protocol version 3.2 (07JAN2018).

Recruiting; the first patient was included on March 10, 2017. The last patient was included on December 11, 2021. Completion of the 90-day follow-up before May 2022 and unblinding and statistical analysis will begin hereafter.

## Abbreviations

CA: Cardiac arrest
CPC: Cerebral Performance Category
CVP: Central venous pressure
eGFR: Estimated glomerular filtration rate
GCS: Glasgow Coma Scale
ICU: Intensive care unit
LAP: Left atrial pressure
LOE: Level of evidence
LVEF: Left ventricular ejection fraction
MAP: Mean arterial pressure
MoCA: Montreal Cognitive Assessment
MRI: Magnetic resonance imaging
mRS: Modified Rankin Scale
NSE: Neuron-specific enolase
OHCA: Out-of-hospital cardiac arrest
PAP: Pulmonary artery pressure
PCI: Percutaneous coronary intervention
PEEP: Peak end-expiratory pressure
Pro-BNP: Pro-brain natriuretic peptide
ROSC: Return of spontaneous circulation
SBP: Systolic blood pressure
TTM: Targeted Temperature Management
